### Secondary Outcomes

Changes to body weight, body mass index, waist circumference, and TCM symptom scores are the secondary outcomes of interest. All the parameters will be assessed during the screening period, at the beginning of the treatment period, and every 4 weeks during the treatment period.

### Biological Specimen Analysis Outcomes

The changes to the composition of intestinal microbiota, gut microbiota metabolites, and blood metabolites will be examined in faeces and blood samples at the beginning and at the end of the 12-week treatment period. The alpha-diversity, beta-diversity, principal components analysis, principal co-ordinates analysis, nonmetric multidimensional scaling, permutational multivariate analysis of variance, the linear discriminant analysis effect size of intestinal microbiota, gut microbiota metabolites, and blood metabolites will be calculated based on 16S rRNA gene sequencing and gas chromatography/time-of-flight mass spectrometry analyses. Further correlation analysis between intestinal microbiota and clinical indexes, intestinal microbiota and gut microbiota metabolites, and intestinal microbiota and blood metabolites will be performed to explore the intervention mechanism.

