## Abstract

**Background:** Type 2 diabetes mellitus (T2DM) complicated with dyslipidaemia is associated with a high risk of cardiovascular diseases. The Jiangtang Tiaozhi (JTTZ) recipe is a Chinese herbal formula that has been used to regulate the blood glucose and lipid levels for many years. Interestingly, a previous study has demonstrated its efficacy; however, the associated mechanism remains unclear. We hypothesised that the therapeutic effect of the JTTZ on patients with T2DM may be mediated by the modulation of metabolites secreted by the gut microbiota. This study aims to examine this mechanism.

**Methods and analysis:** This study is a randomised, positive drug parallel-controlled, open-label clinical trial in patients with T2DM and dyslipidaemia. A total of 96 patients will be recruited and randomly assigned to treatment with JTTZ or metformin for 12 weeks. The primary outcome will be the rates of effectively regulated blood glucose and lipid levels (measured with the levels of glycated haemoglobin, fasting plasma glucose, 2-h plasma glucose, triglyceride, and low-density lipoprotein cholesterol). The secondary outcomes will be the changes in body weight, body mass index, and waist circumference and Traditional Chinese Medicine symptom scores. In addition, 16S rRNA gene sequencing will be performed on the gut microbiota obtained from faeces, and metabolomics analysis will be performed based on blood and gut microbiota samples. Intention-to-treat, per-protocol analysis and safety analysis will be performed.

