Traditional Chinese Medicine (TCM) approaches reportedly improve glycaemic control, blood lipid levels, and weight management. (Wu et al., 2020). In fact, a TCM herbal formula may ameliorate blood glucose and lipid levels by shifting the composition of the gut microbiota. (Tong et al., 2018). The Jiangtang Tiaozhi (JTTZ) recipe has been used to treat patients with T2DM with dyslipidaemia for many years. (Zhao, 2013). Interestingly, the findings from a multi-centre trial suggested that it is safe and effective in the management of the blood glucose levels, lipid levels, and weight in patients with T2DM with obesity and hyperlipidaemia. (Yu et al., 2018). The formula consists of eight Chinese herbs, including Aloe [*Aloe vera* (L.) Burm. f. or *Aloe ferox* Mill. (Asphodelaceae)], *Coptidis rhizoma* [*Coptis chinensis* Franch., *Coptis teeta* Wall., or *Coptis deltoidea* C.Y.Cheng and P.K.Hsiao (Ranunculaceae)], *Anemarrhenae rhizoma* [*Anemarrhena asphodeloides* Bunge (Asparagaceae)], red yeast rice [*Fermentum Rubrum* (Aspergillaceae)], bitter melon [*Momordica charantia* L. (Cucurbitaceae)], *Salvia miltiorrhizae radix et rhizoma* [*Salvia miltiorrhiza* Bunge (Lamiaceae) ], *Schisandrae chinensis fructus* [*Schisandra chinensis* (Turcz.) Baill. (Schisandraceae)], and *Zingiberis rhizoma* [*Zingiber officinale* Roscoe (Zingiberaceae)]. In the TCM theory, the JTTZ recipe clears the excess heat in the stomach and intestines, thus alleviating patients’ symptoms. However, the mechanism underlying the clinical efficacy of the JTTZ recipe remains unknown. We hypothesised that the JTTZ may exert a therapeutic effect equal to or better than that exerted by metformin among patients with T2DM with dyslipidaemia, and that this effect may be mediated by the modulation of metabolites secreted by the gut microbiota. Therefore, a randomised, positive drug parallel-controlled, open-label clinical trial was designed; 16S rRNA gene sequencing as well as gas chromatography/time-of-flight mass spectrometry analyses will be performed to explore these mechanisms.

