**FIGURE 1 F1:**
[figure not shown]
Flow diagram of the study design.

**TABLE 1 T1:** Schedule of enrolment, assessments, and data collection.

Period	Enrolment/Baseline	Allocation	Treatment period			Follow-up period
Time points	Introduction period	0week	4 weeks	8 weeks	12 weeks	48weeks
Eligibility screening	×	—	—	—	—	—
Informed consent	×	—	—	—	—	—
Physical Examination	×	×	—	—	—	—
Characteristic	×		—	—	—	—
Random allocation	—	×	—	—	—	—
Interventions	—	—	×	×	×	—
Clinical Assessments	—	—	×	×	×	—
Medical history	×	×	×	×	×	×
Body weight	×	×	×	×	×	—
Waist circumference	×	×	×	×	×	—
Body mass index	×	×	×	×	×	—
Electrocardiogram	—	×	—	—	×	—
Routine urinalysis	—	×	—	—	×	—
Complete blood count analysis	—	×	—	—	×	—
HbA1c	—	×	—	—	×	×
FPG	×	×	×	×	×	×
2 h-PG	×	×	—	—	×	×
Blood lipid indicators	×	×	—	—	×	×
TCM symptom score	×	×	×	×	×	×
Liver and kidney function	—	×	×	×	×	—
Islet function	—	×	—	—	×	×
Urinary microalbumin	—	—	—	—	—	×
Urinary microalbumin/-creatinine ratio	—	—	—	—	—	×
Cardiac ultrasound	—	—	—	—	—	×
Carotid artery ultrasound	—	—	—	—	—	×
Biological specimens	—	×	—	—	×	—
Adverse event	—	×	×	×	×	—

FPG, fasting plasma glucose; PG, plasma glucose; TCM, traditional Chinese medicine.

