### Interventions

Patients in the JTTZ recipe group will receive the JTTZ recipe granules (30 g per bag), one bag at a time, twice a day, to be taken with warm water after meals. Patients in the metformin group will receive 500 mg metformin tablets at a time, three times a day, to be taken with meals. The allocated interventions may be modified. In addition, this study applies the add-on therapy and the former administration of lipid-lowering agents will not be withdrawn. If AEs or voluntary withdrawal occurs, the interventions will be discontinued. Laboratory tests and drug packing return will be arranged to monitor and improve adherence.

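### On-treatment faecal and blood metabolites are read as microbial in origin, although compounds from the study products, if the assay captures them, would separate the arms with no microbial change

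*Protocol article*

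**What the plan says.** The Abstract and the Background state the mechanistic hypothesis in terms of source. The Background says that "this effect may be mediated by the modulation of metabolites secreted by the gut microbiota", and the Abstract gives examination of this mechanism as the aim of the study.

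The Biological Specimen Analysis Outcomes section gives the measurement. Besides the make-up of the intestinal flora, it says that "gut microbiota metabolites, and blood metabolites will be examined in faeces and blood samples at the beginning and at the end of the 12-week treatment". The stool readout is thus already named as a product of the microbiota. A list of summaries and tests, including principal components analysis, PERMANOVA and LEfSe, is applied to the microbiota and to both sets of metabolites, and these "will be calculated based on 16S rRNA gene sequencing and gas chromatography/time-of-flight mass spectrometry analyses". Correlations between microbiota and metabolites follow, to explore mechanism.

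In Table 1 the row "Biological specimens" is marked at 0 and 12 weeks only. Interventions are also marked at 12 weeks, and no specimen is planned at the 48-week visit.

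Under Interventions, one arm takes "JTTZ recipe granules (30 g per bag), one bag at a time, twice a day" and the other "500 mg metformin tablets at a time, three times a day". The Background lists the eight herbs in the formula.

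**The concern.** The quantity of interest is defined by where a metabolite comes from. The measurement, as described, records what is present in stool and blood. The two agree only if every feature that responds to treatment comes from the microbiota.

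The design gives a specific reason to doubt this. The arms swallow chemically different products, exposure begins after the first sample, and the only later sample is taken at the end of treatment. A compound from the granules or the tablets, or a host breakdown product of one, would follow the randomised arm and the visit. Randomisation cannot remove it, because it is a direct consequence of the allocated treatment.

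At stake is the attribution of an arm difference, not whether there is one. A product-derived feature would give a real difference in stool or blood, and the section as written would credit it to the microbiota. The error would run towards the hypothesis under study.

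**Working it through.** The protocol gives no figure for this point, so there is none to reproduce. The check sets the passages side by side and then asks how few product-derived features would matter.

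**Reading the passages together**

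| Element | What the article fixes | Where |
|---|---|---|
| Construct | metabolites secreted by the gut microbiota | Abstract, Background |
| Measurement | GC/TOF-MS of faeces and blood; targeted or untargeted not stated | Biological Specimen Analysis Outcomes |
| Timing | week 0 and week 12, nothing off treatment | Table 1, same section |
| Exposure | eight-herb granules against metformin tablets | Background, Interventions |
| Use | arm and visit comparisons; correlations with taxa, read as mechanism | Biological Specimen Analysis Outcomes |

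No element separates sources. With no off-treatment sample, timing cannot do so either.

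**Illustration 1: multivariate comparison of arms**

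Inputs: 38 patients per arm (Sample Size, before the dropout allowance). The rest are assumptions: 300 independent, normally distributed features, of which k are drug-derived and shifted by d SD in one arm at week 12; no microbial effect; PERMANOVA on Euclidean distance with 99 permutations at 5%; 150 runs per row.

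| k of 300 | d (SD) | Runs rejecting | Mean R² |
|---|---|---|---|
| 0 | – | 7% | 1.3% |
| 3 | 1 | 57% | 1.6% |
| 3 | 2 | 100% | 2.3% |
| 9 | 1 | 100% | 2.1% |

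The 7% has a Monte Carlo standard error of √(0.067 × 0.933 / 150) = 0.020, so it is compatible with the nominal 5%. Three features are 3/300 = 1% of the panel.

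**Illustration 2: correlation of a taxon with a drug-derived feature, arms pooled**

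The two are independent within each arm. The taxon is shifted by a SD and the feature by b SD in one arm. With equal arms, the pooled correlation is approximately

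r = (ab/4) / √[(1 + a²/4)(1 + b²/4)].

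- a = 0, b = 2: r = 0. Simulated: r about 0.00, significant in 5% of runs.
- a = 0.5, b = 2: r = 0.25 / √(1.0625 × 2) = 0.17. Simulated: 0.17, significant in 32%.
- a = 1, b = 2: r = 0.5 / √(1.25 × 2) = 0.32. Simulated: 0.32, significant in 83%.
- a = 1, b = 1: r = 0.25 / 1.25 = 0.20. Simulated: 0.20, significant in 42%.

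(3,000 runs each, 38 per arm.) A taxon that differs between arms therefore correlates with a drug-derived feature through arm membership alone. Within an arm, the correlation is zero by the set-up.

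Both illustrations are conditional. They show what follows if the assay captures such features. They are no evidence that it does.

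**The case against.** The strongest reply is that this is laboratory detail. Peak annotation, removal of drug-derived peaks and the interval from last dose to sampling are commonly left to a full protocol or analysis plan, and the Data Management section refers to a full trial protocol that is not shown. That stands: their absence is no error. It does not answer the point that the article itself applies a microbial label to an on-treatment measurement that does not identify source.

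The analyses also sit apart from the primary and secondary outcomes, and the Discussion claims only that they may partly reveal the mechanism. That stands too, and it limits the weight of the point.

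A reader might infer more than the documents support:

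- **That the assay detects the study drugs.** The article names the platform but not its scope or library. Detection is plausible for a multi-herb oral product and less certain for metformin by gas chromatography. A purely targeted panel could narrow the concern considerably.
- **That the daily mass of each product measures the problem.** The two quantities differ greatly, but ingested mass says nothing about the number or intensity of detectable features.
- **That product compounds must be absent at week 0.** Inclusion criterion 5 does not require drug-naive patients, and the article describes no washout. Earlier exposure to metformin or herbal products is possible.
- **That the correlations are certainly contaminated.** Illustration 2 needs pooled arms, and the article does not say whether they will be pooled.

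**Conclusion.** The point holds in conditional form. As the specimen section is written, an arm difference in faecal or blood metabolites cannot by itself be attributed to microbial secretion, because samples taken on treatment may contain compounds derived from the products.

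The true size is unknown, since the documents give neither the assay scope nor a feature count. Under the stated assumptions, about 1% of features would be enough for PERMANOVA to reject in 57% to 100% of runs with no microbial effect. The R² would stay small (1.6% to 2.3%, against 1.3% with no drug-derived features), so a low R² would not show that the result was safe. These rejections reflect a true arm difference; the error is in assigning it to the microbiota.

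The point is confined to the metabolite comparisons and the correlations that use metabolites. HbA1c and 16S composition are unaffected. It is a cheap improvement to an exploratory analysis and does not threaten the trial's main result.

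**What to change.** In the Biological Specimen Analysis Outcomes section:

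1. Call the stool readout 'faecal metabolites', and keep microbial origin for the interpretation.
2. Run extracts of the JTTZ granules and of the metformin tablets as reference samples in the GC/TOF-MS batches already planned, and flag matching features.
3. Report the metabolite comparisons and the microbiota-metabolite correlations with and without the flagged features.
4. Report the correlations within arm as well.
5. Specify this before the metabolite data are seen, so that setting aside strong hits is not discretionary.

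Do not exclude features merely because they appear at week 12 in one arm only. That rule could delete a new microbial metabolite induced by one treatment, which is the signal sought.

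Cost: a few extra injections, and no new patients, visits or specimens. Within-arm correlations use fewer patients. By r = t/√(df + t²), the two-sided 5% threshold rises from 1.9925/√(74 + 3.970) = 0.23 with 76 patients to 2.028/√(36 + 4.113) = 0.32 with 38.

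Two limits remain. A true microbial metabolite that also occurs in a product may be flagged, which reporting both ways makes visible. Host or microbial breakdown products of the herbs will not match an extract, so unflagged features are not thereby shown to be of microbial origin. The mechanistic conclusion should therefore stay at association.

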### Adverse Events

AEs will be continuously monitored during the 12-week treatment period and during the 36-week follow-up period. AEs indexes will include electrocardiogram findings, hepatic function tests (i.e., levels of alkaline phosphatase, aspartate aminotransferase, alanine aminotransferase, and g-glutamyl-transpeptidase), renal function tests (i.e., creatinine and urea levels), complete blood count analysis, routine urinalysis, islet function, urinary microalbumin, urinary microalbumin/creatinine ratio, cardiac ultrasound, and carotid artery ultrasound. In addition, AEs in the form of uncomfortable symptoms and other ailments will be comprehensively documented, including the timing of onset, severity, duration, treatment, and outcomes. Each AE associated with the intervention drugs will be classified as mild, moderate, or severe. Severe AEs will be submitted to the principal investigator and ethics committee within 24 h of onset. All AEs will be resolved properly. The Guang’anmen Hospital will cover non-negligent harm associated with the protocol. The AE severity evaluation criteria are as follows: 1) Mild: the patients can tolerate the discomfort, which does not interfere with the treatment, does not require special treatment or affect patient rehabilitation; 2) Moderate: the patients cannot tolerate the discomfort and require special treatment, which may affect their recovery outcomes; and 3) Severe: the patients are at risk of death or disability and require immediate emergency treatment.

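### The text promises adverse-event monitoring through the 36-week follow-up, but the adverse-event row of Table 1 and four other safety rows end at week 12

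*Protocol article*

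**What the plan says.** The Adverse Events section of the protocol article sets the window in one sentence: "AEs will be continuously monitored during the 12-week treatment period and during the 36-week follow-up period". It then names the adverse-event indexes: electrocardiogram, hepatic and renal function tests, blood count, urinalysis, and in addition "islet function, urinary microalbumin, urinary microalbumin/creatinine ratio, cardiac ultrasound, and carotid artery ultrasound". It also asks that symptoms be documented with onset, severity, duration, treatment and outcome.

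Table 1, titled "Schedule of enrolment, assessments, and data collection", has these columns: "Time points Introduction period 0week 4 weeks 8 weeks 12 weeks 48weeks". Week 48 is the single follow-up visit. The row "Adverse event" is marked at weeks 0, 4, 8 and 12 and carries a dash at week 48. The row "Liver and kidney function" has the same pattern. By contrast, "Islet function" is marked at weeks 0, 12 and 48, and "Cardiac ultrasound" at week 48 only.

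The Statistical Analysis section announces a safety analysis and gives no time window for it.

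**The concern.** Two current statements in the same document disagree on when adverse events are collected. One says continuously to week 48; the other ends the adverse-event row at week 12. Both cannot be followed.

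At stake is whether events arising after treatment ends are recorded in a structured way. The Data Management and Quality Control section says that events go onto standardised case report forms and that records are entered after each visit. If those forms were built from Table 1, there would be no adverse-event entry for the follow-up. A 48-week adverse-event count would then combine 12 weeks of visit-based collection with 36 weeks of incomplete ascertainment, and a low count of late events would be hard to interpret. The missing window in the statistical section leaves open which period the safety analysis covers.

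**Working it through.** **Step 1: the stated window.** Inputs from the Adverse Events section: 12 weeks of treatment and 36 weeks of follow-up. 12 + 36 = 48 weeks, which agrees with the last column of Table 1. The text and the table therefore mean the same follow-up, and the difference is not one of definition.

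**Step 2: the share after the last marked adverse-event visit.** The last mark in the adverse-event row is at week 12. 48 − 12 = 36 weeks, and 36/48 = 0.75, or 75% of the stated window.

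**Step 3: the indexes named in the text, read row by row in Table 1.**

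| Row in Table 1 | Weeks marked | Week 48? |
|---|---|---|
| Adverse event | 0, 4, 8, 12 | no |
| Liver and kidney function | 0, 4, 8, 12 | no |
| Electrocardiogram | 0, 12 | no |
| Complete blood count | 0, 12 | no |
| Routine urinalysis | 0, 12 | no |
| Islet function | 0, 12, 48 | yes |
| Urinary microalbumin | 48 | yes |
| Microalbumin/creatinine ratio | 48 | yes |
| Cardiac ultrasound | 48 | yes |
| Carotid ultrasound | 48 | yes |

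The nine rows below the adverse-event row hold the named indexes (hepatic and renal tests share one row). Four end at week 12 and five are measured at week 48: 4 + 5 = 9.

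**Step 4: what the five week-48 indexes can show.** Islet function has values at weeks 0 and 12, so change over follow-up can be judged. The other four (5 − 1 = 4) have a single value at week 48. From the schedule alone, an abnormal finding on one of these four cannot be classed as new, worsened or already present at entry.

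**Step 5: is the dash an artefact of text extraction?** The adverse-event row has all six cells filled, four with a mark and two with a dash. Other rows, such as HbA1c, fasting glucose, medical history and islet function, carry a mark in the week-48 column. The dash reads as a deliberate entry.

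**Step 6: effect of marking week 48.** Table 1 has no visit between weeks 12 and 48, so one added mark would have to cover 36 weeks by recall. That would agree with the stated period, although a single retrospective visit is a thin basis for calling the monitoring continuous.

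**The case against.** The strongest reply is that the mismatch is confined to part of a condensed table. The text itself plans collection during follow-up, asks for full documentation of symptoms, and requires severe events to be reported within 24 hours of onset. Staff were trained in adverse-event reporting. The trial has one centre, and data management is referred to a full protocol and a data management plan that are not shown. Week 48 includes medical history, the TCM symptom score and five of the named indexes. Every visit from the start to the end of treatment has the adverse-event row marked, so the gap lies after treatment.

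Much of this stands. A reader might infer that no adverse-event collection is planned after week 12, or that follow-up would rest on unsolicited reports alone. The documents support neither: the text plans the collection, Table 1 places safety tests and medical history at week 48, and nothing distinguishes solicited from unsolicited reporting. Nor does the article show that staff would follow the table rather than the text, or announce a 48-week safety claim.

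The reply does not remove the contradiction. The article states both positions, so this is not detail left to a fuller document. Medical history is no substitute for the adverse-event row, because Table 1 marks both separately at weeks 0 to 12.

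**Conclusion.** The point holds as an internal contradiction. The text carries adverse-event monitoring to week 48; in Table 1 the adverse-event row, with electrocardiogram, blood count, urinalysis, and liver and kidney function, ends at week 12. For the adverse-event row the uncovered share is 36 of 48 weeks, or 75%. This is calendar time and not a share of events: the documents give no event rate, so the number of events that might be missed cannot be calculated.

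Five named indexes are measured at week 48, but four of them have no earlier scheduled value, which limits what they can say about new onset or change.

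The conclusion assumes that the dash is intended. Any loss of late events further assumes that the case report forms follow Table 1, which the article does not establish. The matter should be corrected, but it does not touch the primary efficacy comparison.

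**What to change.** Reconcile the Adverse Events section with Table 1 in one of two ways.

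1. **Keep the 48-week window.** Mark the adverse-event row at the existing week-48 visit, with adverse-event questions that cover weeks 12 to 48, and state which indexes are repeated there. The cost is one schedule entry and one case report form page at a visit that already takes place, plus the tests themselves if any of the four rows that now end at week 12 are repeated.

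2. **End adverse-event collection at week 12.** Correct the sentence in the Adverse Events section, limit adverse-event counts in the safety analysis to the 12 treatment weeks, and report the week-48 tests as follow-up measurements with no claim of continuous monitoring. Deleting the follow-up clause alone is not enough: urinary microalbumin, its ratio to creatinine and both ultrasounds are listed as adverse-event indexes but measured only at week 48, so their purpose would need restating. The cost is a few sentences of text and the loss of any adverse-event statement beyond treatment.

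Under either option, name the period that the safety analysis covers, and say that the four tests done only at week 48 describe status at that visit and not change.

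### Four measures named as adverse-event indexes are scheduled only at week 48, so a result cannot be classed as pre-existing or treatment-emergent; the week-48 adverse-event cell also conflicts with the text

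*Protocol article*

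**What the plan says.** The Adverse Events section of the protocol article lists the tests that serve as AE indexes. They are the electrocardiogram, liver and kidney function, blood count, routine urinalysis and islet function, followed by "urinary microalbumin, urinary microalbumin/creatinine ratio, cardiac ultrasound, and carotid artery ultrasound". The same section sets the observation window: "AEs will be continuously monitored during the 12-week treatment period and during the 36-week follow-up period". It also asks for each AE associated with the study drugs to be graded as mild, moderate or severe.

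The timing is fixed in Table 1 ("Schedule of enrolment, assessments, and data collection"), whose columns are "Time points Introduction period 0week 4 weeks 8 weeks 12 weeks 48weeks". The rows "Urinary microalbumin", "Urinary microalbumin/-creatinine ratio", "Cardiac ultrasound" and "Carotid artery ultrasound" each carry a mark in the last column and a dash in the other five. The row for adverse events is marked at weeks 0, 4, 8 and 12 and has a dash at week 48.

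**The concern.** A safety index has to show that something arose or worsened after treatment began. One value with nothing before it cannot do that. The trial enrols patients with type 2 diabetes, dyslipidaemia and a raised body mass index or waist circumference, in whom some albuminuria or vascular change before entry is plausible. If such a finding appears for the first time at week 48, nothing in the schedule shows whether it was already there at randomisation. The request to grade events associated with the study drugs calls for a judgement that these four measures cannot inform.

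The timing adds to this. The only assessment comes long after the last dose, so it says little about safety during the 12 weeks of treatment. The table also does not schedule AE recording at the one visit where these tests are done.

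**Working it through.** No figure in the plan needs to be reproduced. The check sets the AE list in the Adverse Events section against the rows of Table 1.

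| AE index | Introduction | Wk 0 | Wk 4 | Wk 8 | Wk 12 | Wk 48 |
|---|---|---|---|---|---|---|
| Electrocardiogram | – | × | – | – | × | – |
| Routine urinalysis | – | × | – | – | × | – |
| Complete blood count | – | × | – | – | × | – |
| Liver and kidney function | – | × | × | × | × | – |
| Islet function | – | × | – | – | × | × |
| Urinary microalbumin | – | – | – | – | – | × |
| Microalbumin/creatinine ratio | – | – | – | – | – | × |
| Cardiac ultrasound | – | – | – | – | – | × |
| Carotid ultrasound | – | – | – | – | – | × |
| *Adverse event row* | – | × | × | × | × | – |

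1. **Baseline.** All five rows in the upper block have a week-0 value and a week-12 value. The four disputed rows have 0 of 5 possible assessments before week 48.
2. **Distance from treatment.** 12 weeks of treatment + 36 weeks of follow-up = week 48. The single assessment is 48 − 12 = 36 weeks after treatment ends.
3. **What can be estimated.** Change from baseline needs two values per patient. With one, no within-patient change exists for any of the four measures. A contrast of week-48 values between the randomised arms can still be formed.
4. **Who contributes to it.** The Sample Size section allows for 20% dropout during follow-up from 48 per arm: 48 × 0.80 = 38.4, so about 38 per arm would be measured if that allowance is used up.
5. **AE capture.** The text has AE monitoring run to week 48. The AE row stops at week 12. Both cannot be right, and the disagreement falls on the only visit with these four tests.

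The four rows are complete, with six cells each, so the pattern is not a table broken in extraction.

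**The case against.** The strongest reply is that little follows from the mismatch. The section says which tests are AE indexes, but not that any abnormal value is recorded as an AE. Its severity scale turns on tolerability, need for special treatment, and risk of death or disability, which a symptomless plaque or mild albuminuria does not obviously meet. Rules for classifying abnormal results may sit in the full trial protocol, which the article mentions and which is not shown. This stands. A reader might infer that existing renal or vascular disease would be counted as AEs, and might put a number per arm on it. The documents support neither step, because they give no counting rule and no prevalence of these abnormalities. The blank AE cell at week 48 points the other way, if anything.

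A reader might also infer that treatment effects on these measures could not be detected at all. That goes too far. Randomisation still supports a between-arm comparison at week 48, limited to patients still followed. What is lost is individual attribution and change from baseline.

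Some mitigation exists. Serious heart and kidney complications are excluded, medical history is taken at every visit, and kidney function, urinalysis and the electrocardiogram have baselines. These would pick up known or advanced disease, but not unmeasured albuminuria or subclinical cardiac or carotid change.

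It does not help to say that the timing is detail left to a fuller document. The article prints an explicit schedule, and that schedule does not fit the use it states for these measures.

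**Conclusion.** The point holds in a limited form. Four of the named AE indexes are measured once, 36 weeks after treatment ends, with no baseline or on-treatment value. They cannot separate pre-existing from treatment-emergent findings in a patient, and they give no within-patient change. The Adverse Events section and Table 1 also disagree on whether AEs are captured at week 48.

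The severity is minor. The four measures are neither primary nor secondary outcomes, the HbA1c comparison is unaffected, and the other listed safety tests have week-0 and week-12 values. The conclusion rests on Table 1 as printed and on no assumption about prevalence. No count of misclassified events is offered, because the documents do not allow one.

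**What to change.** - **Urine measures.** For patients still to be seen, add albumin and creatinine assays to the urine already taken for routine urinalysis at weeks 0 and 12, and mark these in Table 1. The week-48 value then has a baseline and an end-of-treatment value beside it, with no new procedure.
- **Ultrasounds, and urine results without a baseline.** Remove them from the AE indexes. Report them as a descriptive week-48 comparison between the randomised arms, stating how many patients were measured in each.
- **AE capture.** Reconcile the week-48 cell of the AE row in Table 1 with the monitoring period in the Adverse Events section, so that both state the same window.

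The cost is a small assay charge and a few lines of wording. The downside is incomplete coverage. Recruitment was set to run from October 2021 to July 2022, and the documents do not say that urine is stored (the Biological Specimen Analysis Outcomes section names only faeces and blood). Patients already past week 0 will therefore lack a baseline urine value. A week-12 sample alone does not replace it, since it is taken at the end of treatment. For those patients only the descriptive comparison is available.
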